### Analysis of endpoints

The planned analyses are summarized in Table 2. We will use a two-tailed *p* value of 0.05 and report the 95% confidence intervals for all endpoints. In all analyses, we will control for confounders of adherence and retention [7, 48, 49]. In both primary and secondary outcomes, we will undertake per-protocol and intention-to-treat analyses.

**Table 2 Tab2:** Analysis of quantitative outcomes

Outcomes	Measure of outcomes (intervention versus control arm)	Statistical analysis
Treatment success	Proportion of patients with treatment success at six months. Odds ratio of treatment success	Logistic regression, odds ratios
Cure rates	Proportion of patients cured of TB; odds ratio of TB cure	Logistic regression, odds ratios
Treatment completion	Treatment completion rate; odds ratio of treatment completion	Logistic regression, odds ratios
Retention in care	Hazards of attrition in the intervention versus control; Cumulative attrition at six months	Cox’s proportional hazards model, log-rank test
Adherence to TB medicines	Mean adherence rates (proportion of TB medicines)	Mann-Whitney U test and Poisson regression
Appointment keeping and punctuality	Proportion of patients who keep an appointment; Proportion of patients with early, prompt, and late visits	Ordered logistic regression
Drug-resistant TB rates	Proportion of patients with rifampicin-resistant TB	Logistic regression, odds ratios
Call success rates (2,4, and 6 months)	Proportion of successful calls	*t* test

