**Methods:**

We used a theory-based and human-centered design (HCD) to adapt an already piloted software to design “Call for life-TB” (CFL-TB), an MHI that utilizes IVRT to deliver adherence and appointment reminders and allows remote symptom reporting. This open-label, multicenter, randomized controlled trial (RCT), with nested qualitative and economic evaluation studies, will determine the impact of CFL-TB on TB treatment success in patients with drug-susceptible TB in Uganda. Participants (*n* = 274) at the five study sites will be randomized (1:1 ratio) to either control (standard of care) or intervention (adherence and appointment reminders, and health tips) arms. Multivariable regression models will be used to compare treatment success, adherence to treatment and clinic appointments, and treatment completion at 6 months post-enrolment. Additionally, we will determine the cost-effectiveness, acceptability, and perceptions of stakeholders. The study received national ethical approval and was conducted in accordance with the international ethical guidelines.

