### Trial endpoints

The primary endpoint is treatment success (at 6 months): treatment success is a composite outcome, comprising treatment completion and cure in patients with clinically and bacteriologically diagnosed TB, respectively. It is a robust and agreed indicator of treatment success in TB programs. In patients with bacteriologically diagnosed TB, cure is defined as having a negative sputum test in the last month of treatment and on at least one previous occasion [47]. For clinically diagnosed patients, completion entails 6 months of therapy. The denominator for each arm will be the number of patients enrolled. At the same time, the numerator is the sum of bacteriologically and clinically diagnosed patients with cure or treatment completion, respectively.

This RCT also has several secondary endpoints. First, we will determine the TB cure rates in patients with microbiologically diagnosed TB. Second, we will determine treatment completion for patients clinically diagnosed with TB in the two arms: Third, retention rates will be determined and compared between the study arms. Patients will be deemed to be actively engaged in care if they attend a clinic visit within one month of a scheduled appointment. Additionally, we will compare appointments. We will categorize visits as “early,” if they present before an appointment, “prompt” if they show up within three days after the appointment date, “late” if they present after three days but within 30 days of a scheduled appointment and missed if patients do not show up at all or present after 30 days. Fourth, we will determine the incremental costs per additional DALY averted per percentage point increase in treatment success in the intervention versus the control arm. In addition, we will compare adherence rates at months 2 and 6. Depending on the availability of drug susceptibility tests, we will compare the rates of MDR-TB. To understand the impact of the intervention on the treatment outcomes and the potential for adoption and scaling of the intervention, we will explore the perceptions and experiences of patients and care providers towards the MHI. Finally, we will determine the uptake and adherence to the intervention. We will consider the successful receipt of a reminder as a proxy for the utilization of the technology. Therefore, we will determine the proportion of successful calls in the intervention and control arms.

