### Sample size determination

Based on results from a randomized controlled trial in Kenya that demonstrated a 9% increase in TB treatment success following the use of SMS [12], we hypothesize that the interactive voice response platform will lead to at least a 6% higher impact as compared to SMS reminder treatment success (i.e., a 15%-point difference compared to the control arm). A retrospective cross-sectional study of routine data on HIV/TB co-infected patients from the Uganda National Tuberculosis and Leprosy Program reported lost to follow-up rates of 3.5% and 16.6% in urban and rural settings, respectively [7]. The rate of lost-to-follow at the three TB clinics was approximately 11.8%. Therefore, assuming an 11.8% lost-to-follow-up rate, this study would require a minimum of 274 (137 patients per arm) patients to demonstrate a 15% increment in treatment success with a power of 0.8 and precision of 0.05.

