### Analysis of the primary endpoint

We will use logistic regression to determine the crude and adjusted odds ratios of treatment success in the intervention arm versus the control arm. The multivariable model will adjust just for potential confounders, including age, sex, employment status, bacterial load at baseline, TB category, and HIV status [7, 48, 49]. The stepwise backward elimination method will be used to fit the final model. The model with the lowest Akaike information criterion (AIC) statistic will be considered the best fitting. Covariates with a global/trend *p* value > 0.2 at the bivariate analysis, will be adjusted for in the final multivariate model. We will explore factor interactions, including the interaction between age adherence and sputum smear results at baseline. Where interaction is confirmed, we report both the main and interaction effects.

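### Treatment success is to be analysed by intention-to-treat and per-protocol, crude and adjusted, and the protocol does not say which of the four results decides the trial

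*Protocol article*

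**What the plan says.** The endpoint, the arms and the time point are clear: treatment success at 6 months, intervention versus control. Several places in the article bear on how it will be tested.

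- **Populations** (*Analysis of endpoints*): "In both primary and secondary outcomes, we will undertake per-protocol and intention-to-treat analyses".
- **Significance level** (same section): "We will use a two-tailed *p* value of 0.05 and report the 95% confidence intervals for all endpoints".
- **Estimates**: "We will use logistic regression to determine the crude and adjusted odds ratios of treatment success in the intervention arm versus the control arm" (*Analysis of the primary endpoint*).
- **Choice of adjusted model** (same section): "The stepwise backward elimination method will be used to fit the final model". The section adds a lowest-AIC criterion and a bivariate p-value rule.
- **Denominator** (*Trial endpoints*): "The denominator for each arm will be the number of patients enrolled".
- **Adjustment in general**: the Methods part of the abstract says "Multivariable regression models will be used to compare treatment success, adherence to treatment and clinic appointments, and treatment completion at 6 months post-enrolment", and *Analysis of endpoints* says adjustment for confounders applies to every analysis.

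No section ranks the four resulting analyses or says what happens if they disagree. The per-protocol set is not defined in the article.

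**The concern.** Four results will exist for one primary question: intention-to-treat crude, intention-to-treat adjusted, per-protocol crude and per-protocol adjusted. They are correlated but not identical, so near the 0.05 boundary they can disagree. Without a stated ranking, a borderline intention-to-treat result could be reported beside a favourable per-protocol or adjusted one, and the reader could not tell which was meant to answer the primary objective.

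There is also a question of bias. *Participant withdrawal and post-trial care* allows withdrawal after death or disengagement, and data collection then stops. On the denominator in *Trial endpoints* such patients count as non-successes. A per-protocol set that drops them removes part of the very outcome that reminders are meant to change. The distortion can run in either direction.

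**Working it through.** **1. Do the sections settle the choice if read together?**

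| Question | Points one way | Left open by |
|---|---|---|
| Intention-to-treat or per-protocol? | *Trial endpoints*: all enrolled in the denominator | *Analysis of endpoints*: both, side by side |
| Crude or adjusted? | Abstract and *Analysis of endpoints*: adjusted | *Analysis of the primary endpoint*: both |
| Which adjusted model? | Same section lists candidate covariates | Same section selects among them by backward elimination and AIC |

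The lean is towards adjusted intention-to-treat, but a reader has to infer it. The article does label lesser analyses elsewhere: *Analysis of quantitative endpoints* calls a Poisson model a sensitivity analysis, and a *Sensitivity analysis* section lists others. Per-protocol carries no such label.

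**2. The plan's own figure.** The sample-size section asks for 274 "patients to demonstrate a 15% increment in treatment success with a power of 0.8 and precision of 0.05", with 11.8% loss. It gives no control success rate, so 274 cannot be rebuilt from the stated inputs alone. Assuming 0.70 versus 0.85 (mean 0.775), two-sided, no continuity correction:

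n = [1.960·√(2·0.775·0.225) + 0.842·√(0.70·0.30 + 0.85·0.15)]² / 0.15² = 120.5 per arm.

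Dividing by 1 − 0.118 gives 120.5/0.882 = 136.6, so 137 per arm and 274 in total. Rounding up to 121 before inflating gives 138 per arm (276). Success of about 0.70 is therefore a reasonable value for the simulation, but it is an assumption.

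**3. Error rate if any of the four could be claimed.** Four independent tests would give 1 − 0.95⁴ = 0.185. That is only an upper reference, because these tests are strongly correlated.

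The simulation had 274 patients, 1:1, no treatment effect, and intention-to-treat success of about 0.70. Lost patients were failures in intention-to-treat and excluded from per-protocol. There were six covariates of weak to strong effect, four logistic Wald tests, and 6,000 replicates per scenario in the main grid (Monte Carlo error about 0.004). Loss was 3.5%, 11.8% or 16.6%, the rates quoted in *Sample size determination*. Further per-protocol exclusions unrelated to outcome were 0 to 10%.

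| What is left open | Two-sided false-positive rate |
|---|---|
| One named test | about 0.05 |
| Intention-to-treat fixed; crude or adjusted | 0.053 to 0.079 |
| Adjusted fixed; intention-to-treat or per-protocol | 0.061 to 0.093 |
| Any of four, main grid | 0.074 to 0.115 |
| Any of four, 11.8% loss only | 0.090 to 0.112 |

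Raising the outcome-unrelated exclusions to 30% at 11.8% loss gave 0.119, hence the rounded range of 0.07 to 0.12. In favour of the intervention, the any-of-four rate in the main grid was about 0.035 to 0.058 against 0.025. Selecting covariates by AIC in one scenario gave 0.0975 for any of four, within the range above.

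**4. Bias from dropping disengaged patients.** An illustration with assumed figures:

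- Control: 70% success, 20% lost, 10% other failure.
- Intervention: 80% success, 10% lost, 10% other failure.
- All enrolled: 80 − 70 = 10 points.
- Lost patients dropped: 80/90 − 70/80 = 88.9% − 87.5% = 1.4 points.

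A gain that comes entirely through retention almost disappears.

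**The case against.** The strongest reply is that the plan is less open than it looks. The endpoint is defined on all enrolled patients, which a per-protocol analysis cannot use, and the adjustment statements favour the multivariable model. Reporting per-protocol beside intention-to-treat, and crude beside adjusted, is routine. Defining a per-protocol set is commonly left to an analysis plan, and the article refers to a fuller protocol that is not shown. Much of this stands: the lean is real, and the undefined per-protocol set is not held against the plan here. What remains is that the main analysis statement puts per-protocol level with intention-to-treat, at odds with the endpoint's own denominator.

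Two stronger readings are tempting, and the document supports neither.

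- A reader might infer that the trial has four ways to succeed and so doubles its error rate. The protocol states no rule that any one significant result counts as success. The inflated rates describe what follows if such a choice were made.
- A reader might infer that per-protocol will exclude low users of the tool from the intervention arm alone, which could push the error rate much higher. Nothing says so. *Sensitivity analysis* handles tool use by stratifying on utilisation, and any figure for low users would rest on assumed shares and success gaps.

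**Conclusion.** The concern holds as a failure to name the decisive analysis. It is not a finding that the trial's error rate is doubled. If any of the four results could be claimed, the two-sided false-positive rate would be roughly 0.07 to 0.12. If the endpoint's denominator is taken to fix intention-to-treat, the remaining choice between crude and adjusted leaves it at about 0.05 to 0.08. These ranges rest on an assumed success rate of about 0.70, the assumed covariate strengths, the loss rates quoted in the article, and a per-protocol set that drops lost patients plus some others at random. The bias argument does not depend on the error-rate figures. It needs only that per-protocol drops disengaged patients, which is a common definition but not one that the article states. The point should be settled before the database is locked.

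**What to change.** In *Analysis of endpoints* and *Analysis of the primary endpoint*, state that the primary conclusion rests on one test at two-sided 0.05: the intention-to-treat comparison of treatment success at 6 months, on the denominator in *Trial endpoints*, from one logistic model with a fixed list of baseline covariates. The fixed list belongs in the same sentence, because a model selected from the data is not one named test. Label the crude intention-to-treat odds ratio and all per-protocol results as supportive, and say that they cannot establish the primary claim if the named test fails.

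The cost is a short amendment to the protocol or analysis plan, with no new patients or data. The downside is that a favourable per-protocol result can no longer carry the conclusion.

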### Analysis of the primary endpoint

We will use logistic regression to determine the crude and adjusted odds ratios of treatment success in the intervention arm versus the control arm. The multivariable model will adjust just for potential confounders, including age, sex, employment status, bacterial load at baseline, TB category, and HIV status [7, 48, 49]. The stepwise backward elimination method will be used to fit the final model. The model with the lowest Akaike information criterion (AIC) statistic will be considered the best fitting. Covariates with a global/trend *p* value > 0.2 at the bivariate analysis, will be adjusted for in the final multivariate model. We will explore factor interactions, including the interaction between age adherence and sputum smear results at baseline. Where interaction is confirmed, we report both the main and interaction effects.

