#### Inclusion criteria

Evidence of TB diagnosis either confirmed bacteriologically by Xpert MTB/RIF Version G4 assay (Cepheid, Sunnyvale, CA, USA) or clinically diagnosed.Evidence of a personally signed and dated informed consent document that indicates that the participant (or a legal representative) has been informed of all pertinent aspects of the study.Willingness to comply with scheduled visits, treatment plans, laboratory tests, and other study procedures.Aged ≥ 18 yearsMobile phone ownership. Subject to funding, study participants without mobile phones may be provided with mobile phones.Patients who can understand Luganda, Runyankore, Swahili, or English. These languages are the languages spoken by most patients at the study health facilities. If we add Lira RRH as a study site, we will add Luo, the predominant language spoken in the Lango region. Other languages may be added to the service if the anticipated demand surpasses 30 patients.

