### Data collection

At baseline, the staff will obtain sociodemographic data (age, sex, marital status, level of education, employment status, income, transport costs, distance from the facility) and data on TB infection (method of diagnosis, site of infection, and rifampicin resistance at baseline). Prospectively, data will be obtained on adherence, symptoms, sputum tests, missed appointments, and clinic visits (Table 1). Participants will also be interviewed on phone call costs, hospitalization, and over-the-counter treatments. At baseline, we will interview patients (qualitative data) on their anticipated challenges in the use of IVRT and anticipated benefits and challenges. At months 2 and 6, qualitative data will be collected on acceptability and experience with the digital intervention. We will determine the sputum conversion rate at 2 months and cure at 6 months. Chest radiographs will be used to determine the cure for patients with clinical TB. TB cards and treatment registers will be reviewed for death, adherence, and date of patient visits. We will use micro-costing to obtain data on the direct and indirect costs.

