### Sensitivity analysis

To determine the impact of nonadherence to the study intervention, we will stratify the analysis by utilization of the CFL-TB tool. For both primary and secondary quantitative endpoints, we will conduct an overall and stratified analysis by HIV status, TB type (pulmonary versus other forms of TB), and gender.

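### The primary model does not guarantee adjustment for diagnosis type, the baseline factor that decides which success rule a patient must meet

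*Protocol article*

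**What the plan says.** All places are in the Protocol article.

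- **Inclusion criteria.** Patients may be confirmed by Xpert "or clinically diagnosed". The expected mix is not given.
- **Trial endpoints.** Treatment success is a composite, "comprising treatment completion and cure in patients with clinically and bacteriologically diagnosed TB, respectively". For the first component, "For clinically diagnosed patients, completion entails 6 months of therapy". For bacteriologically diagnosed patients, "cure is defined as having a negative sputum test in the last month of treatment and on at least one previous occasion". All enrolled patients form the denominator.
- **Data collection.** Baseline data include "data on TB infection (method of diagnosis, site of infection, and rifampicin resistance at baseline".
- **Randomization, blinding, and allocation concealment.** Allocation slips are prepared per site. No stratification by diagnosis type is described.
- **Analysis of the primary endpoint.** Crude and adjusted odds ratios come from logistic regression. The potential confounders are listed as "including age, sex, employment status, bacterial load at baseline, TB category, and HIV status". Then "The stepwise backward elimination method will be used to fit the final model", with AIC deciding the best fit. A further sentence takes covariates with a bivariate p value above 0.2 into the final model.
- **Sensitivity analysis.** The plan is an overall and "stratified analysis by HIV status, TB type (pulmonary versus other forms of TB), and gender". Pulmonary versus other TB is a different split from confirmed versus clinically diagnosed.

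**The concern.** Take two patients who both finish six months of treatment, neither with the required negative sputum results. The clinically diagnosed patient is a success and the bacteriologically diagnosed patient is not. Diagnosis type thus sets how success is scored, and it is fixed and recorded before treatment can affect it. Such a variable is a natural candidate for a prespecified term in the primary model.

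The article leaves its place in the model to chance in two ways. Diagnosis type is not named as such, and whatever is named can be removed by the selection steps. If it falls out, a chance difference between arms in the share of confirmed patients moves the adjusted estimate as well as the crude one, and some precision is given up although the data are already in hand.

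**Working it through.** **The plan's own figure.** Sample size determination gives 274 (137 per arm) for a 15-point difference, power 0.80, a 0.05 level and 11.8% loss, without a control success rate. It can therefore be approached but not strictly reproduced. Trying 70% versus 85%, two-sided, pooled variance:

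n = [1.96·√(2·0.775·0.225) + 0.842·√(0.70·0.30 + 0.85·0.15)]² / 0.15² ≈ 121 per arm

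121 / (1 − 0.118) = 137.2, so 138 per arm, or 276 in total. This is close to 274, but the 70% is inferred. The calculations below use 137 per arm.

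**Assumed inputs.** The article gives neither the share confirmed (f) nor success by diagnosis type. I take f = 0.50, 0.65 and 0.80, and success gaps of 10, 20 and 30 points between types.

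**Chance imbalance.** SD of the between-arm difference in the share confirmed = √(2f(1 − f)/137). Shift in the crude risk difference = imbalance × gap. For example, at f = 0.50 and a 30-point gap, 1.96 × 6.04 × 0.30 = 3.55 points.

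| f | SD of imbalance (points) | Shift at 1.96 SD: gap 10 | gap 20 | gap 30 |
|---|---|---|---|---|
| 0.50 | 6.04 | 1.18 | 2.37 | 3.55 |
| 0.65 | 5.76 | 1.13 | 2.26 | 3.39 |
| 0.80 | 4.83 | 0.95 | 1.89 | 2.84 |

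An imbalance of 1 SD gives about half of these, 0.5 to 1.8 points.

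**Power.** Logistic regression was simulated with and without a diagnosis-type term (4,000 trials per scenario, 137 per arm, success 65% versus 80% and 70% versus 85%, all three values of f).

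| Gap (points) | Gain over the crude model (power points) | Example |
|---|---|---|
| 10 | about 0 (at most 0.4) | 70% vs 85%, f = 0.65: 84.9% to 85.1% |
| 20 | 0.8 to 1.7 | 70% vs 85%, f = 0.50: 84.8% to 86.5% |
| 30 | 1.6 to 3.1 | 65% vs 80%, f = 0.50: 80.5% to 83.5% |

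The comparator is the crude model. The gain over a model that already holds bacterial load was not computed and may be smaller.

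**What the screen does as written.** With 137 per arm, f = 0.65 and 70% versus 85%, the bivariate p value of diagnosis type exceeds 0.2 in about 25% of simulated trials at a 10-point gap, 0.2% at 20 points and practically never at 30. Read literally, the screen leaves diagnosis type out more surely the more it matters. If the inequality sign is a slip and p below 0.2 was meant, a strong predictor passes the screen, but backward elimination still guarantees no term.

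**The case against.** The strongest reply is that the planned model may already carry this information. The list is open, and it names bacterial load at baseline and TB category. With a level for no bacilli detected, bacterial load would separate most or all clinically diagnosed patients, and TB category could be diagnosis type itself. That stands. A reader might infer that the primary model omits diagnosis type, but the article does not show this. It shows only that inclusion is not assured. Nor is the missing definition of TB category a fault in itself, since a condensed article may leave it to the full protocol or the SAP.

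Second, chance imbalance in a prognostic factor is sampling error already reflected in the confidence interval, and type I error is held without adjustment (null rejection 0.049 to 0.054 in simulation). That stands too: a reader might infer bias, and there is none.

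Third, if diagnosis type predicts strongly, AIC-based elimination would tend to keep it. This is fair as a tendency, but the p-above-0.2 sentence pulls the other way.

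Fourth, a reader might infer that success by diagnosis type goes unreported because it is not among the sensitivity strata. It does not: Research objectives, Trial endpoints, Table 2 and Analysis of quantitative endpoints plan cure in microbiologically diagnosed patients and completion in clinically diagnosed patients, by arm. Those analyses do not, however, adjust the primary estimate.

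What remains is the selection rule, which the article fixes and does not leave open, and which protects no covariate.

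**Conclusion.** The point holds in a limited form. The composite is scored by two rules that depend on a recorded baseline variable, and the stated selection steps do not guarantee that this variable stays in the primary adjusted model. The consequence is avoidable random error: about 1 to 3.6 points in the risk difference at an imbalance of about 2 SD, an extreme met or exceeded in roughly one trial in twenty, against a 15-point target. The gain in power is about 0 to 3 points over a crude model and may be close to nothing if bacterial load already does the work, so a claim that substantial power is being lost would go too far.

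All sizes rest on assumed values for the diagnosis mix (50 to 80% confirmed) and the success gap (10 to 30 points). Different scoring rules do not by themselves establish a gap of any given size. The change is worth making because it is cheap and removes doubt about the primary model.

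**What to change.** In Analysis of the primary endpoint, state that bacteriologically confirmed versus clinically diagnosed, as classified at randomisation, is a fixed term in the primary logistic model, exempt from backward elimination and from any p-value screen. If TB category was meant to be this variable, say so and force it in.

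Code bacterial load with a not-detected level. Clinically diagnosed patients may have no load value, and a complete-case fit could drop them: 20 to 50% of 274, or about 55 to 137 patients, under the assumed mix. If the not-detected level turns out to coincide with clinical diagnosis, one of the two terms is redundant and can be left out without changing the fit.

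The cost is one or two sentences and one degree of freedom, using data already collected. No extra reporting by diagnosis type is needed, since the secondary cure and completion endpoints provide it.

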### Analysis of quantitative endpoints

Logistic regression will be used to determine the adjusted odds ratio for TB cure and treatment completion in the intervention arm versus control arms. We will also determine the predictors of TB cure overall and in both arms. The final model will adjust for age, sex, bacterial load, HIV status, TB site, and symptoms at baseline. We will also determine and compare attrition in the two study arms using the Cox proportional hazards model. We will compute the crude and adjusted hazard rates of attrition in the intervention and control arms. The log-rank test will be used to test for differences in attrition between the study arms. Tests for the Cox proportional hazard assumption will be done graphically using Schoenfeld residuals. The model will adjust for age, sex, Karnofsky score at baseline, HIV status, transport costs, distance from the health facility, TB site, and socioeconomic covariates.

We will compare the mean adherence rates (proportion of TB medicines taken as evidenced by TB card) at 6 months in the intervention and control arms. We will treat adherence as a continuous covariate and compare the median adherence between the intervention and control arms. To compare appointment keeping, we will use ordinal logistic regression to determine the adjusted odds ratios of missed, late, and prompt visits (early used as a reference group). In the sensitivity analysis, Poisson regression will be used to compare the number of missed visits and treatment doses in the intervention and control arms. The models will adjust for age, sex, employment, distance from the health facility, and HIV status. We will use chi-square to compare the proportions of patients with MDR-TB between the two study arms. Additionally, logistic regression will be used to determine the crude and adjusted odds ratios of MDR-TB in the intervention and control arms. Finally, as a proxy for the uptake of intervention and fidelity, we will determine the proportions of successful and dropped and received calls at three different (2, 4, and 6 months) to determine patient exposure and acceptance of the intervention through the study treatment period.

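### The covariate screen for the primary adjusted odds ratio is stated in the wrong direction (p > 0.2) and conflicts, with no order of precedence, with the named covariate list and AIC backward elimination

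*Protocol article*

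**What the plan says.** Everything at issue stands in one paragraph of the protocol article, under Analysis of the primary endpoint.

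- Model: "We will use logistic regression to determine the crude and adjusted odds ratios of treatment success in the intervention arm versus the control arm".
- Named list: "The multivariable model will adjust just for potential confounders, including age, sex, employment status, bacterial load at baseline, TB category, and HIV status".
- Elimination: "The stepwise backward elimination method will be used to fit the final model".
- Criterion: "The model with the lowest Akaike information criterion (AIC) statistic will be considered the best fitting".
- Screen: covariates with a global or trend p "value > 0.2 at the bivariate analysis, will be adjusted for in the final multivariate model".

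Two other places bear on it. Analysis of endpoints makes adjustment general: "In all analyses, we will control for confounders of adherence and retention". Analysis of quantitative endpoints gives the cure and completion models a plain list with no screen: "The final model will adjust for age, sex, bacterial load, HIV status, TB site, and symptoms at baseline". No other section states the 0.2 threshold in the opposite direction, and none says which rule governs.

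**The concern.** A bivariate screen normally lets in covariates that show some association with the outcome, that is, those with a small p value. As written, this one lets in covariates that show none. It also sits beside a list that needs no screening and an elimination procedure that favours small p values. An analyst who follows the text has no single model to fit, and the candidate models differ in the covariates that matter most.

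At stake are the definition of the primary adjusted estimate and, under one reading, the precision that adjustment is meant to buy. The primary endpoint is also less firmly fixed than the secondary cure and completion endpoints, which have a plain list.

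**Working it through.** **Inputs.** From the article: n = 274, 137 per arm, 1:1 allocation, two-sided 0.05, logistic regression, and the rules quoted above. The article gives no covariate effects and no control success rate, so every simulated figure below rests on assumptions. The plan has no figure of its own on this point to reproduce.

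**Step 1: what each rule does with a covariate.** Backward elimination by AIC keeps a term with k degrees of freedom when its likelihood-ratio statistic exceeds 2k. The implied p cut-off is P(chi-square on k df > 2k): 0.157 for k = 1, 0.135 for k = 2, 0.112 for k = 3.

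| Rule | p = 0.01 | p = 0.50 |
|---|---|---|
| Named list | kept if listed | kept if listed |
| AIC elimination (1 df) | kept | dropped |
| Screen as written | not selected | selected |

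The screen uses a bivariate p value and AIC a multivariable one, so the two are not exact opposites, but they are close to it.

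**Step 2: how often each rule selects.** Assumed: six independent standard-normal covariates with log-odds effects per SD of 1.0, 0.7, 0.4, 0, 0, 0; treatment log-OR 0.9; n = 274; 1,500 runs.

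| Covariate effect | p > 0.2 as written | sign reversed | backward AIC |
|---|---|---|---|
| 1.0 | 0% | 100% | 100% |
| 0.7 | 0.1% | 99.9% | 99.9% |
| 0.4 | 17% | 83% | 86% |
| 0 (each of three) | 78–80% | 20–22% | 16–17% |

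The set chosen by p > 0.2 and the set chosen by AIC were identical in 0% of runs. If the two are chained (screen at p > 0.2, then eliminate by AIC), no covariate was left in 94–97% of runs (1,000 runs per setting, normal and binary covariates). The adjusted odds ratio would then simply be the crude one, against the general statement that all analyses control for confounders.

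**Step 3: power if the screen overrides the list.** The rows at 0.4, 0.6 and 0.8 assume three prognostic and three null covariates, a conditional treatment OR of 2.7 and 1,200 runs. The 0.2 row comes from a run with 1,000 replicates and an assumed 70% baseline success. The last row is the setting of Step 2.

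| Assumed log-OR per SD | All fixed | p > 0.2 | Loss |
|---|---|---|---|
| 0.2 | 0.903 | 0.906 | 0.903 − 0.906 = −0.003 |
| 0.4 | 0.893 | 0.867 | 0.026 |
| 0.6 | 0.896 | 0.848 | 0.048 |
| 0.8 | 0.862 | 0.756 | 0.106 |
| 1.0, 0.7, 0.4 | 0.811 | 0.719 | 0.092 |

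The Monte Carlo standard error is about √(0.8 × 0.2 / 1,000) ≈ 0.013 per entry, so the 0.2 row shows no loss. The loss also moves with the other assumptions: with 70% baseline success it was about 2 points at 0.4 (0.912 against 0.891), about 8 at 0.6 and about 10 at 0.8. In the Step 2 setting the crude analysis had power 0.713, so the screen as written recovers almost nothing over no adjustment.

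**Step 4: what is estimated.** In the Step 2 setting the mean log-OR was 0.948 with all covariates fixed, 0.727 under p > 0.2 and 0.719 crude. As odds ratios these are exp(0.948) = 2.58, exp(0.727) = 2.07 and exp(0.719) = 2.05.

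**Step 5: type I error.** With no treatment effect, rejection rates were 0.051 to 0.058 across the crude, screened (either direction), fixed and AIC analyses (1,500 runs). Under the Step 3 covariate assumptions (1,200 runs) they were 0.044 to 0.065.

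**Step 6: reversing the sign.** In the Step 2 setting, power was 0.809 with the screen reversed, 0.815 with AIC and 0.811 with the fixed list.

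**The case against.** The strongest reply is that the symbol is a slip for <. With that corrected, the list can be read as a pool of candidates, and pool, screen, elimination and AIC form a familiar sequence. Step 6 supports part of this: reversing the sign recovers the simulated power. The analysing statistician is blinded to arm, and the crude odds ratio is reported in any case.

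Much of that stands, and it rules out several stronger readings that a reader might infer:

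- *That the plan drops the prognostic covariates.* The sentence says that covariates with p > 0.2 are adjusted for. It does not say that only those are, and it does not cancel the named list. The loss in Step 3 applies only if the screen overrides the list.
- *That there are four incompatible rules.* Elimination and AIC are one procedure, so the screen conflicts with two others.
- *That the treatment effect is biased or false positives are inflated.* Type I error is near nominal under each rule. The gap between 2.58 and 2.07 reflects non-collapsibility: conditional and marginal odds ratios are different quantities. Choosing among rules after seeing results was not simulated; blinding limits that risk but does not remove it.
- *That the power loss itself shows all selection must go.* It does not, given Step 6. The reason to remove selection is pre-specification.

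Two things survive. The published text does state the wrong direction, with no correction elsewhere. And once the sign is reversed, the text still does not say whether the listed covariates are forced in or are open to removal. Nor is this detail left to an analysis plan: the rule is stated, and stated wrongly.

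**Conclusion.** The point holds. The screen is inverted and contradicts two other rules in its own paragraph, so the primary adjusted odds ratio is not uniquely defined. That follows from the text alone and needs no simulation.

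The size of the consequence is conditional. If the screen governs, the adjusted result moves to nearly the crude one, and the power forgone runs from none (weak covariates, 0.2 per SD) to about 10 points (strong ones, 0.8 per SD). All of these figures rest on assumed, independent covariate effects, and show direction and range rather than a forecast for this trial. If the list is kept and the screen only adds to it, no listed covariate is lost. The correction is needed because the primary model is ambiguous, not because a particular power loss has been shown.

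**What to change.** For the primary comparison, delete the p > 0.2 screen and the stepwise/AIC selection. Pre-specify one logistic model with:

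- arm;
- site, because allocation slips are prepared separately for each site (Randomization, blinding, and allocation concealment);
- the protocol's own baseline covariates: age, sex, employment status, baseline bacterial load, TB category and HIV status.

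Retain every term whatever its p value. State how bacterial load is handled for clinically diagnosed patients, who are eligible and may have no value, for example as a category combined with type of diagnosis. Otherwise a complete-case fit could remove them from a model whose endpoint counts all enrolled patients. Check that this category does not duplicate the TB category term.

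Keep the crude odds ratio beside the adjusted one, as already planned, and confine data-driven selection to exploratory predictor models. At the very least, reverse the inequality and state which rule takes precedence.

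The cost is a change of wording: no new data and no change in sample size. The article reports 123 of 274 enrolled at 15 May 2021 and an analyst blinded to arm, so on its own account the change can be made credibly before analysis.
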